#### **Measurement of Secondary Outcomes:**

A qualitative assessment of implementation by pharmacists will be performed with a brief interview using questions that were developed by the SEARCH-AF study. Patient satisfaction will be assessed using the validated Patient Satisfaction with Pharmacists Services questionnaire 2.0.

#### **Healthcare Utilization**

Healthcare utilization (hospitalization, emergency room visits, physician visits, use of laboratory testing, and use of OAC therapy) will be determined by interrogating patient electronic medical record (NETCARE) for study participants for up to 12 months after study enrollment. We will include in our consent form a specific section about accessing patient electronic medical records.

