## **Summary:**

Oral anticoagulation therapy for stroke prevention in AF is safe and effective but under-utilized. Optimal delivery of existing therapies would prevent AF-related stroke. In this study, we will first evaluate pharmacists’ knowledge regarding appropriate use of OAC therapy in AF. We will then evaluate whether active pharmacist intervention could improve evidence-based use of OAC therapy in eligible AF patients. Lastly, we will evaluate the impact of active pharmacist intervention on healthcare utilization to help inform the economic analysis of pharmacist prescribing.

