## **D. METHODS**

**Study Design:** This is a pilot prospective, open-label, randomized controlled trial with early versus late pharmacist intervention. The unit of randomization is the patient.

**Study Setting:** The study will be performed in community pharmacies with at least one pharmacist with independent prescribing authority as identified by the Alberta College of Pharmacists as successfully completed requirements and who have access to electronic medical records.

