## **RCT:**

### **(ii) Intervention: Early versus Delayed (Figure 1):**

Pharmacists will identify eligible participants as 65 years or older AND with one additional risk factor for stroke assessed by brief history and medical record review. The pharmacist will ask about a history of AF and confirm diagnosis by either electrocardiographic (ECG, Holter, event monitor) documentation or by physician documentation (notes or discharge summary). If AF is confirmed and the patient is taking oral anticoagulation appropriately (Table 1, Appendix) then they will be excluded from further participation. Stroke risk factors will also be confirmed based on medical record report or self-report and taking disease-specific medication (Table 3, Appendix).

For participants without a history of AF, the pharmacist will assess rhythm by using a mobile ECG apparatus attached to a smart phone or tablet, which will allow a single lead ECG recording (Alivecor) using two fingers on electrodes for 30 seconds. The single lead ECG recording includes a highly accurate and FDA-approved AF detector (sensitivity 98.5%, CI 92-100% and specificity 91.4%, CI 89-93%). Two ECG recordings will be obtained from each participant and if there is disagreement in the interpretation then a third ECG recording will be obtained. Real-time physician verification will be performed for ECG interpretations of AF. For patients with AF, a 12-lead ECG will be required within 24-48 hours of screening session however randomization will occur based on single lead ECG interpretation.

Participants with unrecognized AF who are eligible for OAC therapy (based on single lead ECG) and those with previously diagnosed AF who should be on OAC therapy but are either not on or their existing OAC prescriptions require adjustment due to, contraindications, or sub-optimal levels will be considered as having 'actionable' AF (Table 1, Appendix).

Participants with 'actionable' AF will be randomized (via a centralized secure website to ensure allocation concealment) in a 1: 1 ratio to either early versus delayed pharmacist intervention after obtaining informed consent.

The early intervention arm will have the following timeline:

[figure not shown]

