At time 0, participants will receive AF education, and pharmacists will complete baseline case report form, blood pressure assessment, prescribe OAC therapy or adjust existing prescription based on guideline algorithms; a summary of management will be kept for pharmacy records and a fax will be sent to the family physician regarding participation of the study. At 4 weeks, all participants taking oral anticoagulants will be seen in the pharmacy and the pharmacist/pharmacy technician will complete a follow-up checklist (Figure 4, Appendix). If this is not possible, the participant will be contacted by telephone. As this is a pragmatic trial, additional follow-ups (in-person/phone) will be scheduled at the discretion of the pharmacist particularly if the patient had initiation of warfarin. The OAC clinic at the Mazankowski Heart Institute will provide support throughout this 3 month period if needed. Final follow-up and collection of close-out medications will occur at 3 months. Cardiologist support will be provided for any questions throughout the study period.

For patients randomized to the delayed intervention arm, during the first 3 months they will serve as a control group and will have a fax sent to their family physician identifying them as having 'actionable' AF and a medication list. The delayed intervention arm will follow the same procedures as the early intervention arm for those participants who did not have OAC optimized by their GP during the control phase. The delayed arm timeline will begin at day 90:

[figure not shown]

**(iii) Follow-up:** All participants will have follow-up after 3 months to assess current therapy by a blinded research staff. Follow-up will also entail review of pharmacy electronic records.

**Primary Outcome:** To determine the difference in proportion of patients receiving optimal OAC therapy at 3 months in those randomized to intervention arm versus control arm.

Optimal defined as a new prescription for OAC in a previously untreated AF or known AF who should be on OAC per guideline recommendations or adjustment of an existing OAC in a prescription.

**Anticipated Results:** The rate of new OAC prescriptions or appropriate changes to existing prescriptions will be higher in the intervention arm compared to the control arm.

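### Healthcare utilization is followed for up to 12 months to show the intervention's impact, but intervention versus usual care is randomised only to day 90; after that the arms compare early with delayed start

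*Protocol*

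**What the plan says.** The design (Protocol, Methods, Study Design) is a pilot "randomized controlled trial with early versus late pharmacist intervention", with patients allocated 1:1.

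The Summary gives the purpose of the utilization data: to "evaluate the impact of active pharmacist intervention on healthcare utilization to help inform the economic analysis" of pharmacist prescribing. The Healthcare Utilization section names the measures (hospital admissions, emergency visits, physician visits, laboratory tests, anticoagulant use), to be read from the electronic record "for study participants for up to 12 months after study enrollment".

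The section on early versus delayed intervention limits the control condition. Of the delayed arm it says that "during the first 3 months they will serve as a control group", while the family physician is notified by fax. Then: "The delayed arm timeline will begin at day 90". The delayed arm follows the early arm's procedures, but only "for those participants who did not have OAC optimized by their GP during the control phase".

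Sample size and Statistical Analysis applies intention to treat to all analyses and plans a descriptive comparison of the two groups across the outcomes. It gives no time window for utilization. Nowhere does the Protocol say how data after day 90 enter the comparison.

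**The concern.** The aim, the data window and the delayed-start design are each fixed in the Protocol, and they do not fit together. The aim is the effect of the intervention. The window runs to 12 months. The group that would show what happens without the intervention begins to receive it after 3.

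Followed as written, the by-arm comparison would mix two questions: intervention against usual care up to day 90, and early against delayed start afterwards. The delayed arm's own start-up contacts and tests would also fall inside its 12 months and be counted against the early arm's. If the resulting difference were used as the effect of pharmacist prescribing, the economic analysis could understate both the resources the intervention uses and what it saves.

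**Working it through.** The Protocol states no effect size, power or sample size for utilization, so there is no figure of its own to reproduce on this point. Its sample size belongs to the 3-month primary outcome and does not depend on the utilization window.

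**Inputs.** Window: up to 12 months (Healthcare Utilization). Control period: 3 months, with the delayed arm starting at day 90 (early versus delayed intervention section). Crossover: only controls not optimised by their physician (same section). Enrollment and randomisation are treated as the same day, which is an assumption.

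**Step 1: share of time.** With a full 12-month record:
- Intervention versus usual care: 90/365 = 24.7% (3/12 = 25%).
- After the delayed arm's start: (365 − 90)/365 = 275/365 = 75.3% (9/12 = 75%).

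Because the window is *up to* 12 months, 75% is the maximum for the second share. A participant with 6 months of record would have 3/6 = 50%.

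**Step 2: partial crossover.** Let *q* be the share of the delayed arm not optimised at day 90, and assume that all of them then receive the intervention. Delayed-arm time free of the pharmacist intervention is (3 + 9(1 − q))/12:

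| q (assumed) | pharmacist-free share of 12 months |
|---|---|
| 100% | 25% |
| 75% | 44% |
| 51% | 62% |
| 25% | 81% |

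The 51% row borrows the Protocol's 49% control rate as the share optimised by the physician; it is not a forecast for this trial.

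Pharmacist-free time is not the same as contrast. If the effect were constant per month and equal in everyone, the table would also give the share of the 12-month effect that remains. If instead the effect works through optimal anticoagulation, physician-optimised controls differ little from their early-arm counterparts after day 90. The contrast then lies in the un-optimised share, who are the ones offered the intervention. With a constant monthly effect, roughly 3q/12q = 25% remains whatever *q* is.

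**Step 3: how the effect builds.** Let E(t) be the cumulative effect t months after starting. If all controls cross over at month 3, the 12-month difference is E(12) − E(9), as a share of E(12):
- Constant per month, E = t: (12 − 9)/12 = 25%.
- One-off start-up burden (visits, tests), complete well within 9 months: about 0%.
- Effect growing as t²: (144 − 81)/144 = 44%.

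The listed measures need not share one profile. Step 1 follows from the Protocol; Steps 2 and 3 rest on assumptions and show only that the dilution could range widely.

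**The case against.** The strongest reply is that the criticised analysis is not spelled out. The Healthcare Utilization section describes data collection, the Summary says only that the results help inform an economic analysis, and the comparison window for a non-primary outcome is often left to a statistical analysis plan, which is not shown here. The listed secondary objective on cost concerns the cost of the intervention, which needs no 12-month difference between arms. The longer record also has legitimate uses, such as describing utilization after pharmacist initiation.

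This stands in part: the Protocol does not commit to a single 12-month contrast, and a later plan could restrict it. But the Protocol itself pairs an aim about the intervention's impact with a window that mostly follows the delayed arm's start, and its analysis text compares the groups across outcomes with no time limit. That is a mismatch between stated elements, not just missing detail.

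Two stronger readings are tempting and unsupported. A reader might infer that no randomised contrast exists after day 90. Participants stay in their randomised groups and the declared design is early versus late, so that comparison remains valid and is not biased for its own question. A reader might also infer a 75% attenuation. That requires a constant monthly effect and, unless the effect acts only through un-optimised controls, full crossover; the Protocol establishes neither.

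A further fair point concerns the remedy. A 90-day window captures start-up visits and tests but only the first months of any reduction in admissions, so alone it could tilt the economic picture towards cost.

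**Conclusion.** The point holds in a limited form. The randomised comparison of intervention with usual care covers at most the first 90 of up to 365 days, about 25% of a full window. Beyond that the arms estimate early versus delayed start with partial crossover. A by-arm difference over 12 months is therefore not an estimate of intervention versus usual care. Taken as one it would tend to be diluted, by an amount the Protocol does not allow one to fix.

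The conclusion assumes that the utilization comparison follows the general analysis text and that the delayed arm's crossover goes ahead as described. It concerns a secondary, economic aim. The 3-month primary comparison ends as the delayed arm's intervention begins and is not affected, nor is the sample size.

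**What to change.** In Healthcare Utilization, define the intervention-versus-usual-care comparison of utilization and cost as events from randomisation to day 90, before the delayed-arm visit. Report the by-arm result up to 12 months separately, label it *early versus delayed start*, and state that it does not enter the economic analysis as the effect of pharmacist prescribing against usual care. Give the share of the delayed arm that crossed over beside it.

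The record pull is unchanged and no data are discarded; only wording changes. The price is fewer events and wider intervals in the 90-day window, which sees start-up use more fully than later benefit. That should be stated as a limitation of the economic result.

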## **D. POSSIBLE PROBLEMS AND MITIGATING STRATEGIES**

- 1) This is the first study to evaluate pharmacist prescribing for OAC therapy which may lead to hesitation or apprehension between pharmacists and primary care physicians. In order to overcome potential barriers, our stakeholder team will address potential issues through face-to-face meeting, teleconferences and email correspondence. Stakeholder team members will liaise with their respective communities regarding this study.
- 2) One of the challenges for any study is enrollment. We believe it is feasible to enroll our target sample size as prior Alberta pharmacist-based interventions have

successfully enrolled similar sample sizes. In addition, we will implement strategies based on experiences from the research team ([name], [name], [name]) conducting the Program for the Identification of Actionable Atrial Fibrillation – In the Pharmacy Setting (PIAAF-Pharmacy).

## **E. STUDY IMPORTANCE**

No interventions for AF have been shown to improve survival and reduce serious morbidity beyond OAC therapy for stroke prevention. Effective and safe therapies exist to prevent AF associated stroke. This research will generate new knowledge on an innovative, and potentially sustainable stroke prevention strategy to increase evidence-based use of OAC therapy in patients with AF. These results will help to inform legislative and regulatory bodies in other provinces at various stages of expanding the scope of pharmacist practices and be a leader for other countries (UK, New Zealand, US) with existing independent or collaborative prescribing pharmacists.

## **II. TRIAL MANAGEMENT STUDY ORGANIZATION**

### **A. Central Coordinating Centre**

The study will be coordinated by the SPOR/EPICORE center. EPICORE will be responsible for the electronic CRF, contracts, database and statistical support.

## **B ETHICAL STANDARDS**

### **B.1 Ethical Considerations**

#### ***Ethics Approval***

This study will be conducted in compliance with the protocol, principles laid down in the Declaration of Helsinki, Good Clinical Practice (GCP), as defined by the International Conference on Harmonization (ICH), and ISO standards where applicable. Before study initiation, the Investigator must have written and dated approval/favorable opinion from the Institutional Review Board (IRB) for the protocol and consent form.

Amendments to the protocol will also require IRB approval where applicable and in accordance with local laws and regulations.

#### ***Patient Consent***

Prior to patient participation, written informed consent must be obtained from each patient (or legally accepted representative) and comply with the Declaration of Helsinki. The original signed consent must be retained on file by the Investigator and a copy given to the patient.

#### ***Risk Benefit Analysis***

There are potential risks to patients participating in this study related to the use of OAC therapy including bleeding. An Ontario-based survey evaluating patient's values and

317 preferences regarding relative importance of preventing stroke avoiding bleeding found  
318 patients were willing to endure 4.4 major bleeds in order to prevent one stroke. In  
319 addition, we would be increasing appropriate use of OAC therapy for stroke prevention  
320 concordant with the AF guidelines leading to benefit for the participant of the study.

## 321 **B.2. Patient Confidentiality**

322 All patient information will be stored on a high security computer system and kept strictly  
323 confidential. Subject confidentiality will be further ensured by utilizing subject  
324 identification code numbers to correspond to outcome data in the computerized files.

325 Individual subject medical information obtained as a result of this study is considered  
326 confidential and disclosure to third parties is prohibited except for the following reason;  
327 Medical information may be given to the subject's personal physician or to other  
328 appropriate medical personnel responsible for the subject's welfare.

## 329 **C DATA HANDLING AND RECORD KEEPING**

330 Study personnel at participating sites will complete electronic case report forms (e-  
331 CRFs) through accessing a computerized program via the internet and entering the  
332 required trial information directly into the e-CRFs for electronic submission to a server  
333 located at VIGOUR. Consent forms will be filed at the Investigator's site and made  
334 available for study related monitoring, audits, IRB review and any regulatory inspections  
335 if required. The Investigator must retain all study records in accordance with applicable  
336 regulatory requirements. A Data Management Plan will be developed by EPICORE and  
337 outline the detailed strategies to ensure quality in data collection and reporting.

|                                     |                                                                                                                                                                                                                                                                                                                                                                                                                                                                                                                                                                                                                                                                                                                                                                                                                                                                                                                                                                                                                                                                                                                                  |
|-------------------------------------|----------------------------------------------------------------------------------------------------------------------------------------------------------------------------------------------------------------------------------------------------------------------------------------------------------------------------------------------------------------------------------------------------------------------------------------------------------------------------------------------------------------------------------------------------------------------------------------------------------------------------------------------------------------------------------------------------------------------------------------------------------------------------------------------------------------------------------------------------------------------------------------------------------------------------------------------------------------------------------------------------------------------------------------------------------------------------------------------------------------------------------|
| Actionable AF (non-valvular) | 
Unrecognized AF
 
Previously diagnosed AF not on oral anticoagulation (OAC) therapy but eligible
 
Previously diagnosed AF but require adjustment due to contraindication, or sub-optimal levels
 
 
- Warfarin : average INR not between 2-3 in last 2 months
 
- Rivaroxaban: not on 20 mg daily or 15 mg po daily for CrCL 30-49ml/min or patients with CrCL < 30ml/min taking any dose of rivaroxaban
 
- Dabigatran: not on 150 mg po bid or 110 mg po bid (in patients <math>\geq</math> 75 years or CrCL 30-50ml/min) or patients with CrCL < 30ml/min taking any dose of dabigatran
 
- Apixaban: not on 5 mg bid or 2.5 mg bid (for patients with 2 of the following: age <math>\geq</math> 80 years, body weight <math>\leq</math> 60 kg or serum creatinine <math>\geq</math> 133umol/L) or patients with CrCL < 25ml/min taking any dose of apixaban
 
 
CrCl formula (for Cr measure in umol/L): <math>CrCl = (140 - \text{age})(\text{weight in kg}) \times 1.23</math> (x 0.85 if female)/SerumCr (umol/L)
 |
|                                     | 
For patients with a previous diagnosis of AF this should be confirmed by medical record report (notes, discharge summary, cardioversion) or electrographic evidence (ECG, holter, event monitor, echocardiogram)
                                                                                                                                                                                                                                                                                                                                                                                                                                                                                                                                                                                                                                                                                                                                                                                                                                                                                                          |

| Recruitment Strategies |                                                                                                                                                                                                                                                                                                                                                                                                                                                                                                                                                                                                                                                                                                                                                                                                                                                                                                                                                                                                                                                                                                                                                                                                                                              |
|------------------------|----------------------------------------------------------------------------------------------------------------------------------------------------------------------------------------------------------------------------------------------------------------------------------------------------------------------------------------------------------------------------------------------------------------------------------------------------------------------------------------------------------------------------------------------------------------------------------------------------------------------------------------------------------------------------------------------------------------------------------------------------------------------------------------------------------------------------------------------------------------------------------------------------------------------------------------------------------------------------------------------------------------------------------------------------------------------------------------------------------------------------------------------------------------------------------------------------------------------------------------------|
| Advertising            | Local newspapers; senior community associations; senior events                                                                                                                                                                                                                                                                                                                                                                                                                                                                                                                                                                                                                                                                                                                                                                                                                                                                                                                                                                                                                                                                                                                                                                               |
| In-store               | 
Posters
 
Stand with an iPad near blood pressure kiosk with Alivcor technology for rhythm detection and prompt to see pharmacist
 
Verbal notification by pharmacist of patients who present for any prescription
 
Pharmacist/technician query database for age <math>\geq</math> 65 years AND any of the following on medication review to send invitation to attend screening session:
 
 
i) anti-arrhythmics (ie amiodarone, sotalol, flecainide, propafenone, disopyramide)
 
ii) digoxin
 
iii) ca channel blocker (ie. verapamil, diltiazem, norvasc)
 
iv) b-blocker (ie metoprolol, bisoprolol, carvedilol, atenolol)
 
v) ace-inhibitor (ie. lisinopril, ramapril)/angiotension receptor blocker (ie. cozaar, losartan, diovan)
 
vi) thiazide (hydrochlorthiazide), lasix, spironolactone
 
vii) any glucose lowering medication
 
 
biguanides (ie metformin)
 
sulfonylureas (ie glyburide, glipizide)
 
meglitinides (ie repaglinide)
 
thiazolidinediones (pioglitazone)
 
DPP-4 inhibitors (ie sitagliptin)
 
alpha-glucosidase inhibitors (ie acarbose, miglitol)
 
insulin
 |

|                                            |                                                                                                                                                                                                                                                                                                                                                                                                                             |
|--------------------------------------------|-----------------------------------------------------------------------------------------------------------------------------------------------------------------------------------------------------------------------------------------------------------------------------------------------------------------------------------------------------------------------------------------------------------------------------|
| Hypertension                        | 
Medical record report (ie notes, discharge summary) of a diagnosis of hypertension
 
Or self-report and taking at least one of the following class of drugs: ace-inhibitor (ie.lisinopril, ramapril);angiotension receptor blocker (ie. cozaar, losartan, diovane);thiazide (hydrochlorthiazide); ca channel blocker (ie. verapamil, diltiazem, norvasc);b-blocker (ie atenolol, metoprolol, bisoprolol)
 |
| Diabetes                            | 
Medical record report (ie notes, discharge summary) of a diagnosis of diabetes
 
Or self-report and taking at least one of the following class of drugs: biguanides (ie metformin); sulfonylureas (ie glyburide, glipizide);meglitinides (ie repaglinide); thiazolidinediones (pioglitazone); DPP-4 inhibitors (ie sitagliptin); alpha-glucosidase inhibitors (ie acarbose, miglitol)
                    |
| Heart Failure                       | 
Medical record report (ie notes, discharge summary) of a diagnosis of heart failure
 
Or Cardiac imaging with left ventricular ejection fraction <math>\leq 0.40</math>
 
Or self-report and taking loop or thiazide diuretics
                                                                                                                                                                             |
| Stroke or Transient Ischemic Attack | 
Medical record report (ie notes, discharge summary) of a diagnosis of Stroke or Transient Ischemic Attack
 
Or Brain imaging (CT or MRI) with previous infarct
                                                                                                                                                                                                                                                  |

